### Planned statistical analysis

Statistical significance will be assumed at p < 0.05. Normality of the data will be assessed via Kolmogorov-Smirnov testing complemented by visual inspection of QQ plots and histograms. Normally distributed data will be presented as mean (±SD), non-normally distributed data will be presented as median (±IQR).

The effect of high-fidelity simulated gravity (1, 0.7, 0.5, 0.38, 0.27 and 0.16g) upon lower limb internal kinetics (i.e., joint reaction forces) when walking, running, and skipping at speeds ranging between 0.53–3.6 m/s will be determined by a Two-Way Repeated Measures ANOVA with:

Independent variables: six simulated gravity conditions; 10 locomotion trials (see Table 1)Dependent variables: Joint reaction forces of the hip, knee, and ankle

The effect of high-fidelity simulated gravity (1, 0.7, 0.5, 0.38, 0.27 and 0.16g) upon lower limb internal kinetics (i.e., joint reaction forces) during candidate plyometric movement (i.e., maximal ankle hopping, maximal effort countermovement jumping, and drop-jumps/landings) will be determined by a One-Way Repeated Measures ANOVA with:

Independent variables: six simulated gravity conditionsDependent variables: Joint reaction forces of the hip, knee and ankle

In case the assumption of sphericity has been violated–i.e., Mauchly’s test statistic is significant (p<0.05)–the Geisser-Greenhouse correction will be used to determine the effect of the independent variables on the dependent variables. If a significant effect of the simulated gravity condition, the locomotion trial, or the interaction between simulated gravity condition and locomotion trial is found, Bonferroni corrected post-hoc t-tests will be employed.

Alternatively, if data has a non-normal distribution the non-parametric Friedman test with Dunn’s post-test will be used.

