#### Sample size

As to our knowledge there are no directly comparable published data, a sample size estimation was performed based on the results of a pilot study conducted at the L.O.O.P. GBF. During this pilot study, a single participant performed submaximal single-leg hopping at 2 Hz (using a metronome) for 30 seconds under five simulated gravity conditions (1, 0.5, 0.37, 0.25, 0.17g). For each session, peak vertical joint reaction forces were calculated for the hip, knee and ankle using the same simulation framework as described in this protocol (see *“Planned Data Analysis”)*.

Using this simulation framework, means and standard deviations of the peak vertical joint forces of the hip, knee and ankle were calculated and extracted for each gravity condition, which were used to calculate the Cohen’s *d* effect sizes based on the mean difference and pooled standard deviations [48]. These data were then used in an *a priori* power analysis to estimate a required sample size of 21 (S1 File) using G*Power (version 3.1.9) [49] with: t-test (matched pairs), α = 0.05, Power = 0.95, two-tailed. In order to ensure adequate data collection, we estimate a maximal data loss of 25%, therefore our sample size target will be 26 participants.

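### The rule for correcting the gravity-by-trial interaction depends on a Mauchly test that cannot be computed with 26 participants

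*Protocol article*

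**What the plan says.** All of this is in the protocol article, under Planned statistical analysis and Sample size.

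- For walking, running and skipping, the effect of gravity on hip, knee and ankle joint reaction forces "will be determined by a Two-Way Repeated Measures ANOVA". The factors are "six simulated gravity conditions; 10 locomotion trials". Table 1 confirms ten trials: 3 walking, 2 skipping and 5 running.
- Sphericity is handled conditionally: "In case the assumption of sphericity has been violated", which the article defines as "Mauchly’s test statistic is significant (p<0.05"), then "the Geisser-Greenhouse correction will be used to determine the effect of the independent variables on the dependent variables".
- The interaction is a planned test. As with either main effect, where "the interaction between simulated gravity condition and locomotion trial is found, Bonferroni corrected post-hoc t-tests will be employed".
- Each plyometric movement has a one-way repeated-measures ANOVA over the six gravity levels.
- The target is 26 participants, 21 of them required by the power calculation. The article adds: "we estimate a maximal data loss of 25" per cent.

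The article does not say what happens if Mauchly's test is unavailable, or how a participant with an empty cell is treated.

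**The concern.** A significant Mauchly test is the only stated trigger for the correction. Mauchly's statistic needs a contrast covariance matrix of full rank, so there must be more participants than contrasts. That holds for the main effects but not for the interaction.

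The interaction shows whether the effect of gravity on joint load differs by gait and speed, and it opens the way to post-hoc tests at three joints. If its trigger cannot be evaluated, someone must choose between the corrected and uncorrected result after the data are in. The two can differ materially when the cells are correlated or unequal in spread.

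**Working it through.** **Inputs.** Six gravity levels, ten trials and the 0.05 level come from Planned statistical analysis; 26, 21 and 25% come from Sample size. The covariance patterns are assumptions, because the article gives none.

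**The plan's own figure.** 21 × 1.25 = 26.25, rounded to 26. This reproduces the target. A full 25% loss leaves 26 × 0.75 = 19.5, so 19 whole participants.

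**Contrasts.** Gravity 6 − 1 = 5; trial 10 − 1 = 9; interaction 5 × 9 = 45.

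**Rank.** The sample covariance S of p contrast scores from N participants has rank at most min(N − 1, p).

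| N | Gravity (5) | Trial (9) | Interaction (45) |
|---|---|---|---|
| 26 | 5 | 9 | 25 |
| 21 | 5 | 9 | 20 |
| 19 | 5 | 9 | 18 |
| 46 | 5 | 9 | 45 |

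**Mauchly's statistic.** W = det(S) / (tr(S)/p)^p. For the interaction at N = 26, 21 or 19, det(S) = 0, so W = 0 and the test has no p-value. Full rank needs N − 1 ≥ 45, that is N ≥ 46. For both main effects and the plyometric ANOVAs (5 contrasts), W exists at every N shown.

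**What can still be computed for the interaction.** With m the mean contrast vector, F = N·m′m / tr(S), on 45 and 45 × 25 = 1125 degrees of freedom at N = 26. Epsilon = tr(S)² / (45·tr(S²)). Neither needs S to be invertible. At N = 26 the estimated epsilon cannot exceed 25/45 = 0.556, and in simulation it averages 0.35 even when sphericity is true (true value 1). The corrected test is therefore conservative.

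**Does the choice matter?** Interaction test, N = 26, no true interaction, nominal 5%, 1,500 to 4,000 replicates per run; a range means more than one run.

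| Assumed covariance | Uncorrected | Always corrected |
|---|---|---|
| Spherical | 4.4–5.7% | 0.4–0.5% |
| SD proportional to gravity or load | 8–11% | 1.4–1.6% |
| Serial correlation 0.5 | about 10% | about 1.7% |
| Serial correlation 0.8 | 16–17% | 3–4% |
| Correlation 0.8 and proportional SD | about 20% | about 5% |

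**Empty cells (side point, assumed rates).** Classical repeated-measures ANOVA uses participants with all 6 × 10 = 60 cells. If cells were lost independently at rate c, the expected number complete is 26 × (1 − c)^60: 19.2 at 0.5%, 14.2 at 1% and 7.7 at 2%.

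**The case against.** **The analysis still runs.** A reader might infer that the whole two-way ANOVA cannot be carried out. The documents do not support that. The stated aim is the effect of gravity, and its Mauchly test exists, as do the one for trial and those for the plyometric analyses. The interaction F and its epsilon can also be computed. Only one trigger fails. This objection stands in full.

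**The correction might cover the whole model.** The wording speaks of the independent variables in the plural, so a significant Mauchly test for either main effect could be read as switching on the correction everywhere. That is a possible reading, and it means an uncorrected interaction is not certain. It does not rescue the rule: sphericity of the main-effect contrasts says nothing about that of the 45 interaction contrasts. If both main-effect tests were non-significant, the interaction would again go uncorrected.

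**The inflation is assumed.** Correct. Under sphericity there is essentially none, and no document supplies a covariance.

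**Missing cells.** A reader might also infer that one failed trial deletes a participant, and that failures cluster at extreme gravity and speed and so bias the complete cases. The article states neither. It is condensed, and missing-data handling may sit in a fuller plan. Each locomotion trial lasts at least a minute while the simulation needs one movement cycle, so a failed cycle need not empty a cell. The 25% is an allowance on participant numbers, not a cell-failure rate. This part is no finding against the article.

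**Conclusion.** The concern holds for one test. As written, the sphericity rule cannot be evaluated for the gravity-by-trial interaction at 26 participants, nor at 21 or 19. This follows from the plan's own numbers and needs no assumption. Taken literally, an absent p-value is not below 0.05, so the uncorrected F would stand.

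The size of the consequence does rest on assumptions. False-positive rates are about 8 to 17% under moderate to strong serial correlation or a spread that scales with gravity, about 20% with correlation 0.8 and proportional spread combined, and near 5% under sphericity. Some departure from sphericity is plausible, since the cells run from slow walking at 0.16g to running at 3.61 m/s at 1g, but its degree is unknown.

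The Friedman test with Dunn's post-test, the stated alternative for non-normal data, does not close the gap, because it does not test an interaction.

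**What to change.** Delete the Mauchly condition and state that the Geisser-Greenhouse correction is applied to every repeated-measures effect or, at a minimum, always to the gravity-by-trial interaction. This is a change of wording, needs no new data, and should be made before results are seen. Its price is power: the corrected interaction test is conservative at this N, so a non-significant interaction should not be read as evidence that gravity acts alike across gaits and speeds.

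Optionally, add as a sensitivity analysis a linear mixed model on all available cells, with participant-level bootstrap or cluster-robust inference, so that results do not depend on participants having all 60 cells. For the joint interaction test the bootstrap is the safer choice: a cluster-robust covariance built from 26 participants has rank at most 26, so a 45-degree-of-freedom Wald test meets the same limit. A mixed model with only a random intercept and gravity slope should not become the primary analysis, because its model-based tests assume that the remaining within-person errors are independent. The cost is modest extra modelling work.

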The association between (simulated) hypogravity (0g < *g* < 1g) and the reduction of external kinetics has been investigated. For instance, studies conducted in the L.O.O.P. (Locomotion On Other Planets) Facility at the University of Milan demonstrated reduced external work when walking, running and skipping at speeds ranging between 0.56 and 3.6 m/s representing gait speeds observed in simulated hypogravity using vertical body weight support, compared to 1g [15, 16]. Furthermore, hip, knee and ankle net joint moments have been shown to decrease in proportion with simulated hypogravity during walking [17]. Similarly, previous work performed as part of the MoLo programme (MoLo VTF) reported peak vertical GRFs to be scaled to simulated gravity levels (0.7, 0.38, 0.27 and 0.16g) during sub-maximal plyometric hopping on a vertical suspension system [18].

On the ISS and thus in μg, ‘gravity replacement loading systems’ are employed during exercise in an attempt to maintain external kinetics, including GRFs. Whilst comprehensive evaluation of external kinetics during exercise on the ISS has yet to be performed, 1g GRFs are not replicated on the T2 treadmill [19–21], or the Advance Resistive Exercise Device (ARED) [22] due to engineering and restraint system tolerability issues. The failure to replicate 1g equivalent external kinetics is also reflected in lower joint kinetics [17], and other indices of ‘internal’ musculoskeletal kinetics and thus ‘loading’, i.e., forces and moments acting on bones, joints, muscles and tendons [17, 23, 24]. However, due to the low number, methodological heterogeneity and potential bias of currently available studies, the relationship between movement in hypogravity and internal kinetics remains unknown [23].

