MSK modelling is used to represent skeletal anatomy and muscle-tendon unit physiology, including geometry, contraction dynamics, and neural control, and characterise human movement [32]. When combined with optimisation techniques, musculoskeletal modelling is used to predict muscle activation patterns, and estimate internal kinetics, which is currently not directly measurable in vivo [32]. This approach has allowed researchers to distinguish between clinical populations [33, 34], and grade exercises according to their joint kinetic (loading) profile [35]. Yet, to our knowledge, only two hypogravity computational studies have been performed. The first evaluated a lower extremity assistive device for resistance training in microgravity [36]. The second predicted preferred locomotion strategies at low gravity levels and revealed three distinct locomotion strategies [37]. In 1g, walking was–unsurprisingly–predicted as the preferred locomotor strategy up to 2 m/s, while at Martian gravity, running was predicted to be most energy-efficient. In Lunar gravity however, skipping was predicted to be the optimal strategy–consistent with that frequently observed during Apollo missions [37–39]. However, neither of these studies reported muscle-tendon unit forces, nor joint reaction forces.

On Earth, the plyometric-like mechanics of skipping have been shown to result in greater vertical GRFs than running at the same speed [15, 37]. Although one study has shown that the peak forces borne by the knee are lower during skipping than during running at the same speed [40], which suggests that the proposed benefit of plyometric-like movements on musculoskeletal loading do not manifest at the joint level. However, McDonnell and colleagues [40] used a musculoskeletal model that assumed muscles produce force proportional to physiological cross-sectional area, and do not account for neural input nor force-length-velocity relationships. Ignoring activation and contraction dynamics have been shown to produce non-physiological, instantaneous changes in force estimations during ballistic movements, which can lead to an over-reliance on muscles with large physiological cross-sectional area. To better understand the benefit of plyometric-like movements to hypogravity exercise countermeasures, it is important to achieve physiologically realistic muscle estimations.

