#### T1 –Data collection session

After placing all motion capture markers and sensors on the participant’s body (see *“Study Hardware”*), each participant will perform a short, pre-defined warm-up (five-minute walking at their preferred walking speed in 1g, fifteen submaximal ankle hops and five submaximal countermovement jumps in 1g).

Before the experimental dynamic trials, static motion capture calibration will be conducted with participants quietly standing on the instrumented treadmill centrally within the motion capture volume in a T-pose (arms outstretched horizontally) for five seconds. All participants will then be exposed to a randomised sequence of simulated gravities (1, 0.7, 0.5, 0.38, 0.27, 0.16g). For each gravity level, the conditions for the locomotion trials (i.e., walking, running and skipping) at various defined speeds (Table 1), and plyometric movement trials (i.e., maximal ankle hopping, maximum effort countermovement jumping, and drop-jumps/landings) will also be performed in a randomised order (Fig 1).

**Table 1 pone.0278051.t001:** Conditions of the locomotion trials.

*Locomotion Style*	Speed (m/s)						
	0.56	1.11	1.39	1.94	2.50	3.06	3.61
Walking	X	X	X				
Skipping				X	X		
Running			X	X	X	X	X

All locomotion trials (walking, running and skipping) at each gravity level will be performed for at least one minute in a randomized order at speeds previously shown (Table 1) to facilitate analysis of joint internal loads and muscle-tendon unit behaviour and in relation to the cost of transport curve as a function of speed and gravity [15, 16].

All plyometric movement trials will be performed in the gravity conditions in a randomized order:

Vertical hopping will be performed in a single ramp-up-ramp-down trial consisting of 30 consecutive hops ascending from very shallow (<5cm) to maximal jump height, and then descending back to starting target height. Audio feedback (i.e., increasing and decreasing pitch) guiding hopping height will be provided similar to that used in our pilot study on the verticalized treadmill facility [18].Three maximal effort vertical countermovement jumps separated by at least 10 seconds.Three drop-jumps/landings separated by at least 10 seconds.

Self-selected rest periods will be encouraged between trials to minimise fatigue, and any discomfort associated with wearing the harness.

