### Summary

This study describes a protocol for the first time where a unique vertical body weight support system will be used to simulate, in high-fidelity, several locomotor and plyometric movements at a variety of gravity levels, including those resembling Lunar (0.16g) and Martian (0.38g) gravities. To our knowledge, this will be the first time such a facility has been used to simultaneously collect state-of-the-art movement kinetics, kinematics, muscle activation and muscle-tendon behaviour in a range of hypogravity conditions. Using these data as inputs within a computational musculoskeletal modelling and optimisation framework, we will estimate lower limbs internal kinetics (i.e., joint reaction forces) which is critical to gain a better understanding and prediction of hypogravity-induced musculoskeletal adaptations. Integration of muscle-tendon behaviour within the musculoskeletal modelling will significantly advance the understanding of the importance of forces generated through muscular contractions for preserving musculoskeletal health in low gravity environments. Such insights on the relationship between movement in hypogravity and internal loads will be key to inform on future mitigation strategies and prevention of detrimental adaptations due to prolonged exposure to hypogravity but will also be crucial to guide Lunar surface extravehicular activity (EVA) operations, and EVA suit and habitat ergonomics.

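### Gravity enters the analysis only as six unordered levels, so no trend of joint load on gravity gets a confidence interval; planned trend and matched-speed contrasts would be a cheap addition

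*Protocol article*

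**What the plan says.** *Planned statistical analysis* in the protocol article targets "The effect of high-fidelity simulated gravity (1, 0.7, 0.5, 0.38, 0.27 and 0.16g) upon lower limb internal kinetics". For locomotion this "will be determined by a Two-Way Repeated Measures ANOVA with" the factors "Independent variables: six simulated gravity conditions; 10 locomotion trials (see Table 1"). For each plyometric movement it "will be determined by a One-Way Repeated Measures ANOVA with" the same six gravity conditions as the only factor. A significant effect leads to Bonferroni-corrected post-hoc t-tests. Non-normal data go to Friedman's test with Dunn's post-test. Data are to be summarised as mean (SD) or median (IQR).

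Table 1 defines the ten trials: walking at 0.56, 1.11 and 1.39 m/s, skipping at 1.94 and 2.50 m/s, and running at 1.39, 1.94, 2.50, 3.06 and 3.61 m/s.

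The Introduction gives the gap as "the relationship between movement in hypogravity and internal kinetics remains unknown". The Summary promises: "Such insights on the relationship between movement in hypogravity and internal loads will be key". The formal main aim under *Objectives* is narrower: to estimate joint reaction forces at ankle, knee and hip.

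**The concern.** The six gravity levels are known, unequally spaced numbers. The ANOVA, the post-hoc tests and the Friedman fallback would all give the same result if those numbers were replaced by six arbitrary names. The planned inference can say that some levels differ and which pairs reach significance. It does not say how fast joint load changes per unit of gravity, with what precision, or whether the change is straight or curved.

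Two things are at stake. If the response is close to linear, a 5-df test spends power on patterns that are not there. And a list of corrected pairwise tests will usually show neighbouring levels as not significant even when load falls steadily, which invites reading a plateau at the low, Lunar end.

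A smaller matter concerns gait. The ten-level trial factor carries gait and speed together, so its main effect does not isolate gait. The Introduction cites a study in which "the peak forces borne by the knee are lower during skipping than during running at the same speed", and Table 1 contains the cells for such a comparison, but they are not singled out.

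**Working it through.** **Inputs from the article.** Gravity levels 1, 0.7, 0.5, 0.38, 0.27 and 0.16g. Paired t-test, two-sided alpha 0.05, power 0.95, required n = 21, target 26 (*Sample size*).

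**Assumptions.** The article prints no effect size (it points to S1 File, which is not shown) and does not say which gravity pair or joint supplied it. I take one joint and one movement, means linear in g, exchangeable errors, and the implied effect placed on 1g v 0.16g. The last of these is varied in step 5.

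**1. The plan's own figure.** Solving the noncentral t for 95% power at n = 21 gives dz = 0.828, and n = 21 is required for any dz from about 0.828 to 0.850. This shows that the stated n is consistent with such an effect; it does not reproduce it independently.

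**2. Omnibus v linear contrast.** Take the SD of a paired difference as the unit, so the error variance per observation is 1/2.
- Mean g = 3.01/6 = 0.502; S = sum of squared deviations = 0.473.
- Slope b = dz/(1 − 0.16) = 0.828/0.84 = 0.985 per g.
- Noncentrality = n·b²·S/(1/2) = 2 × 21 × 0.985² × 0.473 = 19.3.
- Omnibus: noncentral F on 5 and 5 × 20 = 100 df.
- Linear contrast with its own error: noncentral t on 20 df, noncentrality √19.3 = 4.39.

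| dz for 1g v 0.16g | n | Omnibus | Linear |
|---|---|---|---|
| 0.83 | 21 | 93% | 98.7% |
| 0.83 | 26 | 97.5% | 99.7% |
| 0.6 | 21 | 65.6% | 85.7% |
| 0.5 | 21 | 48% | 71% |

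**3. Pairwise follow-up at n = 21.** Six levels give 6 × 5/2 = 15 pairs. The article does not state the number of comparisons, so 15 is an assumption. Alpha per test = 0.05/15 = 0.0033, and dz for a pair = 0.828 × gap/0.84.
- 1 v 0.16g: dz 0.828, power 67%.
- 1 v 0.7g: dz 0.296, power 4.3%.
- 0.7 v 0.5g: dz 0.197, power 1.7%.
- 0.5 v 0.38g: dz 0.118, power 0.8%.
- 0.38 v 0.27g and 0.27 v 0.16g: dz 0.108, power 0.7% each.

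**4. Other response shapes at n = 21** (assumed means, in the same units, from 1g down to 0.16g).
- Flat, then falling (0, 0, 0, −0.3, −0.6, −0.83): omnibus 98.6%, linear 98.4%. No gain.
- Inverted U (0, 0.4, 0.83, 0.83, 0.4, 0): omnibus 99%, linear alone 18%.
- All variation in participants' slopes: the Geisser-Greenhouse-corrected F reduces to the trend test, both about 95%. No gain.

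**5. The same dz on a narrower gap** (b = 0.828/gap, n = 21).
- 1 v 0.27g: linear 99.8%, omnibus 98.1%.
- 1 v 0.38g: 99.99% v 99.8%.
- 1 v 0.5g: both above 99.9%.

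The omnibus loss is then 0 to 2 points. The 0.27 v 0.16g pair stays weak: its dz is at most 0.828 × 0.11/0.5 = 0.182, giving 1.5% power at the Bonferroni level. The 1 v 0.7g pair rises to as much as 18%.

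**6. Gait and speed.** Table 1 fills 3 + 2 + 5 = 10 of 3 × 7 = 21 gait-by-speed cells. The cells matched on speed are walk v run at 1.39 m/s and skip v run at 1.94 and 2.50 m/s.

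**The case against.** The best defence is that nothing here is wrong. Repeated measures ANOVA tests the stated target, an effect of gravity. Six level means per joint and trial describe load against gravity without assuming a shape. The formal aim is to estimate joint forces; no slope is promised. Shape-free coding suits a setting where the Introduction reports distinct gait strategies by gravity level and a complex link between external and internal forces. All of this stands. A reader might infer that the relationship goes unestimated or that the ANOVA is invalid, and the article supports neither.

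The power loss also depends on assumptions that the article does not settle, as steps 4 and 5 show. That stands too. A reader might claim a loss of about 35 points for the interaction (5 × 9 = 45 df v 9 df for slope-by-trial: 44% v 79%). That uses a noncentrality of 16 that comes from no document; at 5, 40 and 60 the difference is about 14, 7 and 0.5 points. It also assumes that all of the interaction lies in the slopes.

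On gait, one ten-level factor is a reasonable coding because Table 1 cannot be fully crossed, and the matched-speed pairs are within reach of the post-hoc tests. What remains is that they have no planned place of their own. The phrase "as a function of speed and gravity" under *T1 – Data collection session* might be read as promising a load curve. It refers to a cost-of-transport curve from cited work and does not help the point.

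Last, an article may leave contrasts to an analysis plan. But this one names its model, follow-up and fallback, so the point concerns a stated choice rather than missing detail.

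**Conclusion.** The point holds as a cheap improvement, not as an error. The article frames its question as a relationship in the Introduction and Summary, fixes an analysis that ignores the order and spacing of gravity, and so plans no trend with a confidence interval.

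The efficiency gain is about 6 points for the omnibus test at n = 21 if means are near linear and dz 0.83 belongs to 1g v 0.16g. It is about 20 points if that dz is 0.6, about 2 points at n = 26 with dz 0.83, and small or nil in the other cases worked above. The risk of misreading a steady fall as a plateau is less sensitive to where dz is placed, because low-gravity neighbours have very low corrected power in every linear case examined.

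The results do not support replacing the factorial ANOVA or its full interaction with a linear model. That would be a trade-off, and it would fail for a non-monotone response.

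**What to change.** In *Planned statistical analysis*, keep both ANOVAs, including the full gravity-by-trial interaction, and add:

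- Linear and quadratic contrasts on the actual values 1, 0.7, 0.5, 0.38, 0.27 and 0.16g for each joint and movement, each with its own error term. Report the slope with a 95% CI, and use the remaining gravity df as a lack-of-fit test.
- Slope-by-trial (9 df) as an additional test beside the 45-df interaction.
- A small planned family of three matched-speed contrasts: walk v run at 1.39 m/s, and skip v run at 1.94 and 2.50 m/s.
- A statement that any speed term is nested within gait, because Table 1 is not fully crossed.

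The cost is wording and a few extra tests on data already planned, with no added participants or trials. The linear term must be read together with the quadratic and lack-of-fit results, above all for maximal jumps, where a non-monotone response is possible. The additions should be fixed before the outcome data are analysed; chosen afterwards, they lose confirmatory standing.

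### The stated 95% power is for one uncorrected paired t-test, but every paired t-test in the analysis is Bonferroni-corrected, so that power does not apply to them

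*Protocol article*

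**What the plan says.** **Sample size.** The protocol article (Sample size) takes its effect sizes from a pilot in which "a single participant performed submaximal single-leg hopping at 2 Hz" under five gravity levels. They are described as "effect sizes based on the mean difference and pooled standard deviations", for the hip, knee and ankle. The calculation is a "t-test (matched pairs), α = 0.05, Power = 0.95, two-tailed", described as a "power analysis to estimate a required sample size of 21". The article then says "we estimate a maximal data loss of 25%, therefore our sample size target will be 26 participants". It mentions no multiplicity adjustment. The effect size itself is left to the S1 File.

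**Analysis.** Planned statistical analysis specifies a two-way repeated-measures ANOVA for locomotion, with factors "six simulated gravity conditions; 10 locomotion trials", and a one-way repeated-measures ANOVA over the six gravity levels for the plyometric movements. The dependent variables are the joint reaction forces of three joints. If gravity, locomotion trial or their interaction is significant, "Bonferroni corrected post-hoc t-tests will be employed". The section does not state how many comparisons the correction covers, nor does it limit them to comparisons with 1g.

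**The concern.** The two sections do not fit together. The sample size rests on a paired t-test at alpha 0.05, and no planned paired t-test is run at that alpha. A reader who takes the 95% at face value would apply it to the reported comparisons, such as 0.16g against 1g at one joint. A non-significant corrected result could then be read as evidence that loading is preserved in hypogravity, when the test had much less than 95% power to show a difference of the size planned for. The article intends its results to inform the design of Lunar exercise countermeasures, so that reading would matter.

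The point concerns two things the article fixes, the test behind the power figure and the correction applied to the tests, and not the absence of detail.

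**Working it through.** **Inputs from the article.** N = 21; alpha 0.05 two-tailed; power 0.95; matched-pairs t-test; target 26; six gravity levels; ten locomotion trials (Table 1: three walking, two skipping, five running).

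**Assumed input.** The effect size is not in the text, so it is solved from the stated N, alpha and power. Here dz is the mean paired difference divided by the SD of the differences.

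**Formula.** With df = n − 1 and noncentrality dz × √n, power = P(T > t_crit), where T is noncentral t and t_crit is the 1 − alpha/(2m) quantile of t for m Bonferroni comparisons (alpha = 0.05). The opposite tail is negligible.

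**Step 1: the article's own figure.** At n = 21 and m = 1, t_crit = 2.086. Power is exactly 95% at dz = 0.828 (noncentrality 0.828 × √21 = 3.79). At dz = 0.850, n = 20 already reaches 95%. So 21 is the smallest adequate N for dz from 0.828 up to 0.850. This shows what the stated figures imply. It does not check the unseen input.

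**Step 2: possible families.**
- Each hypogravity level against 1g: 5
- Those five plus the same-speed gait pairs in Table 1 (walk v run at 1.39 m/s; skip v run at 1.94 and 2.50 m/s): 5 + 3 = 8
- All gravity pairs: 6 × 5 / 2 = 15
- All locomotion-trial pairs: 10 × 9 / 2 = 45
- Gravity pairs within each locomotion trial: 15 × 10 = 150

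**Step 3: power per comparison at alpha 0.05/m.** Each range runs from dz = 0.828 to dz = 0.850.

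| m | alpha per test | n = 21 | n = 26 | detectable dz (95% power, n = 21) |
|---|---|---|---|---|
| 1 | 0.05 | 95–96% | 98–99% | 0.83 |
| 5 | 0.01 | 82–84% | 91–93% | 1.01 |
| 8 | 0.00625 | 76–79% | 88–90% | 1.06 |
| 15 | 0.00333 | 67–71% | 82–85% | 1.12 |
| 45 | 0.00111 | 51–55% | 70–73% | 1.24 |
| 150 | 0.000333 | 35–38% | 54–58% | 1.37 |

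**Step 4: after data loss.** A 25% loss from 26 leaves 26 × 0.75 = 19.5. With 19 or 20 analysable, power for 15 pairs is 60–67%.

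**Step 5: N for 95% power at the same effect, before data loss.** 29–30 for five contrasts, 34–35 for 15 pairs, 45–47 for 150 pairs. All exceed 21, and all exceed 26.

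**The case against.** - **The 67% is not a ceiling.** A reader might infer that power cannot exceed 67%. The documents do not support that. If all 26 participants are analysable, 15 pairs keep 82–85%, and five contrasts keep 82–84% even at n = 21. This stands.
- **The family is not stated.** A reader might count all pairs of the 6 × 10 = 60 cells, 60 × 59 / 2 = 1,770, for which power at n = 21 would be 12–14%. The article does not say that all cell pairs will be tested, so this is only an extreme reading. For the same reason it cannot be said that the correction is spent on irrelevant pairs. A condensed article may also leave the list of comparisons to a fuller document. This stands too, but every family of five or more considered here falls below 95%, at n = 21 and at n = 26.
- **The effect size is unseen.** The figures hold for a contrast whose true effect equals the design value. The article does not say which joint or gravity contrast produced 21. If the smallest effect was used, other contrasts do better: at dz = 1.0, power for 15 pairs is 87% at n = 21 and 96% at n = 26. This stands as a limit on the size. It gives no assurance of a margin, because the pilot had one participant doing submaximal hopping.
- **The gravity effect is first tested by ANOVA.** A reader might infer that the whole study is underpowered. The calculation here does not cover the omnibus test and says nothing about its power. The sample-size section does not size for that test either.
- **No contrasts are named in the objectives.** They are to collect data and estimate joint forces. Choosing contrasts with 1g is therefore a recommendation, not the correction of an error.

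**Conclusion.** The mismatch is real. The 95% applies to one uncorrected matched-pairs t-test, and all planned paired t-tests are Bonferroni-corrected follow-ups to repeated-measures ANOVAs. On the back-solved dz, the smallest family considered (five contrasts with 1g) loses 11 to 13 percentage points against the stated 95% at n = 21, and all 15 gravity pairs lose 24 to 28.

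The size rests on three assumptions: the dz range implied by N = 21, a true effect equal to the design value, and correction within one joint and one analysis. Correcting across the three joints as well would lower power further. The direction rests on none of these, since testing the same effect at a smaller alpha with the same n always gives less power.

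**What to change.** 1. Define the post-hoc family before results are seen. The preferred choice is each of the five hypogravity levels against 1g, with Holm adjustment. State whether the family is formed per joint, and whether it is repeated within each locomotion trial.
2. Report all other pairs, including the three same-speed gait pairs, as estimates with confidence intervals.
3. Restate power, or the detectable dz, at the adjusted alpha for the family actually chosen. At n = 21 and dz 0.828 this is about 0.82 (detectable dz 1.01) for five contrasts, or about 0.76 (dz 1.06) if the three gait contrasts join the family. These use the Bonferroni alpha, which is Holm's strictest step, so Holm does no worse. If contrasts are repeated within each trial the figure is lower: five contrasts in each of ten trials, taken as one family of 50, give about 0.50. The 0.82 should not be quoted for a larger family than five.

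**Cost.** Only the wording of the analysis and sample-size sections changes, with no extra data collection. Pairs outside the named set lose their confirmatory tests, and the stated power becomes less favourable.
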